## Abstract

**Background:**

Injury incidence and prevalence in running populations have been investigated and documented in several studies. However, knowledge about injury etiology and prevention is needed. Training errors in running are modifiable risk factors and people engaged in recreational running need evidence-based running schedules to minimize the risk of injury. The existing literature on running volume and running intensity and the development of injuries show conflicting results. This may be related to previously applied study designs, methods used to quantify the performed running and the statistical analysis of the collected data. The aim of the Run Clever trial is to investigate if a focus on running intensity compared with a focus on running volume in a running schedule influences the overall injury risk differently.

**Methods/design:**

The Run Clever trial is a randomized trial with a 24-week follow-up. Healthy recreational runners between 18 and 65 years and with an average of 1–3 running sessions per week the past 6 months are included. Participants are randomized into two intervention groups: Running schedule-I and Schedule-V. Schedule-I emphasizes a progression in running intensity by increasing the weekly volume of running at a hard pace, while Schedule-V emphasizes a progression in running volume, by increasing the weekly overall volume. Data on the running performed is collected by GPS. Participants who sustain running-related injuries are diagnosed by a diagnostic team of physiotherapists using standardized diagnostic criteria. The members of the diagnostic team are blinded. The study design, procedures and informed consent were approved by the Ethics Committee Northern Denmark Region (N-20140069).

**Discussion:**

The Run Clever trial will provide insight into possible differences in injury risk between running schedules emphasizing either running intensity or running volume. The risk of sustaining volume- and intensity-related injuries will be compared in the two intervention groups using a competing risks approach. The trial will hopefully result in a better understanding of the relationship between the running performed and possible differences in running-related injury risk and the injuries developed.

**Trial registration:**

Clinical Trials NCT02349373 – January 23, 2015.

## Background

In modern society, running has become a popular way to exercise and the proportion of adults who participate in recreational running has been growing since the 1970s [1]. In surveys of participation in leisure time physical activity, running is reported to be one of the most popular forms of exercise [2–4] and a national report from the Danish Institute for Sports Studies, estimates that 31 % of the adult population in Denmark participate in recreational running [5]. Running is a cheap and easily accessible form of exercise, and the positive effects of running on health outcomes such as weight loss, cardio respiratory function and mortality are well known [6–8]. Unfortunately, running is also associated with the risk of sustaining a running-related injury. A recently published systematic review and meta-analysis by Videbæk et al. report, that the incidence of running-related injuries per 1000 h of running varies between 2.5 and 33.0 and estimates a weighted injury incidence among recreational runners of 7.7 (95 % CI 6.9 – 8.7) [9]. The knee, lower leg and ankle/foot are the most common sites of injury and a recent study revealed the median time to recovery from injury to be 72 days [10–13]. In addition, the proportion of injured runners receiving conservative treatment was 10.7 %, while 4.7 % underwent surgical treatment [10].

People engaged in recreational running or choosing running as a new and active lifestyle, should be offered evidence-based advice on running schedules with minimal injury risk. Running with a minimized risk of injury would aid the choice of an active lifestyle by decreasing discontinuation from running and, possibly, further reduce the proportion of people at risk of chronic diseases.

Training errors are recognized as a risk factor for running-related injuries and in order to develop running schedules with a minimized risk of injury, a better understanding of the different training variables’ influence on injury risk is needed [14, 15]. Trials investigating differences in injury risk in relation to the progression in running volume, the frequency and duration of running and participation in a preconditioning programme, have been conducted [16–18]. The GRONORUN 1 and 2 trials both mentions the application of an subjective measure of running intensity as a limitation in the trials [19, 20]. The study by Pollock et al.[18] used maximal oxygen uptake as a relative measure of running intensity, comparing different durations of running and different weekly running frequencies. However, the sample consisted of male prison inmates between 20 and 35 years of age, which makes it difficult to generalize the results to recreational or novice runners. A review by Nielsen et al. concluded that there are moderate evidence suggesting that volume is associated with injury risk, but that this association possibly is influenced by the weekly progression in volume and the maturation of the runners [15]. The existing literature on running intensity and the development of injuries show conflicting results, possibly related to the subjective measure used in previous studies [15]. A possible association between the focus of a running schedule and the risk of sustaining specific injuries has also been hypothesized. Specifically, patellofemoral pain, illiotibial band syndrome and patellar tendinopathy were hypothesized to be distance-related, while achilles tendinopathy, gastrocnemius injury and plantar fasciitis were hypothesized to be pace-related [21]. Findings from both experimental and cohort studies support this hypothesized association. In an experimental study by Petersen et al. [22], an increase in running speed resulted in an increase in the peak plantar flexion moment, which was significantly higher than the increase in the peak knee extensor moment (*p* < 0.05). In another experimental study by Petersen et al. [23], a decreased running speed resulted in a cumulative load at the knee joint which was significantly higher, compared with the cumulative knee joint load at higher running speeds [22, 23]. An observational study by Nielsen et al. [24], with a 1-year follow-up and 847 novice runners included, investigated the progression in volume and found that greater progression in running volume increased the risk of the above mentioned distance-related injuries, but not the overall risk of injury. The aim of the Run Clever trial is therefore to conduct a training schedule intervention trial, comparing a running schedule which focus on running intensity with a running schedule which focus on running volume, with the purpose of extending the above mentioned studies, by investigating the difference in risk between the two training variables and the risk of sustaining specific injuries associated with a specific training variable. The following hypotheses are tested (H).Runners with a focus on running intensity have a 15 % increased risk of injury compared with runners with a focus on running volume.A running schedule focusing on intensity, increase the risk of sustaining achilles tendinopathy, gastrocnemius injuries and plantar fasciitis compared with hypothesized distance-related injuries.A running schedule focusing on running volume, increase the risk of sustaining patellofemoral pain syndrome, illiotibial band syndrome and patellar tendinopathy compared vwith hypothesized pace-related injuries.A positive excess risk due to interaction exists between running intensity and running volume, and the effect is more pronounced for pace-related injuries with greater changes in speed than volume, while the effect is more pronounced for distance-related injuries with greater changes in volume than in speed.

Furthermore, complementary risk factor analysis on BMI, age, gender, previous injury, running experience and general activity level will be performed. Of interest is the effect modification of the mentioned risk factors on the interventions’ influence on injury risk. Explorative analyzes will be performed on data collected using the Oslo Sports Trauma Research Center Questionnaire [25]. The focus of the explorative analyzes is the reported physical complaints progressing to time loss injuries and the relationship with the running performed.

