## Methods/design

The Run Clever trial is a randomized trial with a 24 - week follow-up. The follow-up period is divided into an 8 - week *Preconditioning* period and a 16 - week *Intervention Training* period. The randomization is performed after the 8 - week preconditioning period (Fig. 1). Participants are randomly allocated into two intervention groups, following different running schedules: Schedule Intensity (Sch-I) and Schedule Volume (Sch-V). The main outcome is injury and the physiotherapists diagnosing injured participants (diagnostic team) are blinded to group allocation.

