#### Preconditioning period

All included participants follow the same running schedule during the 8 week preconditioning period. The running frequency is 3 running sessions per week, the progression in running volume follows the outlined structure of the 4-week cycle and all running will be performed at an intensity equal to an easy or moderate pace.

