#### Intervention training period

*Sch*-*I* (Intensity training group) is exposed to increased running volume at a hard pace (defined as an intensity equal to or above a VO2max of 88 %). The total running volume per week is fixed, and only kilometers at a hard running pace follow the progression in running. The running volume at a hard pace will increase in each 4 week progression cycle (Fig. 2). The remaining distance will be performed at an easy pace (defined as an intensity below a VO2max of 80 %).

*Sch*-*V* (Volume training group) is focused on increasing the total running volume per week. All scheduled running will be performed at either an easy or moderate pace (defined as an intensity equal to or below a VO2max of 88 %). Only the total running volume per week follows the progression in running (Fig. 2).

The intervention in both groups is presented in Fig. 2 and Tables 1, 2 and 3.

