### Statistical analysis

All data will be analyzed using an instrumental variable approach in the primary analysis [36]. The instrumental variable is the randomization. Secondary analyzes are intention-to-treat and per-protocol. Time to first injury is analyzed using the following primary time scale: calender time in days and weeks. Data will be analyzed at the following time-points: 2 weeks, 4 weeks, 8 weeks and 16 weeks after randomization. Secondary time scales are cumulative running volume in kilometres and cumulative running volume in minutes. Time of follow-up begins when the randomized interventions start. The unit of analysis is each participant. Participants will be right-censored in case of pregnancy, disease, lack of motivation, non-running-related injury causing a permanent stop of running, unwillingness to attend clinical examination in case of injury, if more than 10 % of all training sessions were uploaded manually (they will be censored at the time 10 % of uploads are manual) or at end of follow-up, whichever comes first.

The injury proportion as a function of the follow-up time scales mentioned above will be estimated using the Kaplan-Meier curve. The cumulative injury risk difference between groups is analyzed, performing a generalized linear regression, using the pseudo values method [37]. Competing risk analysis will be performed separately for both groups, to investigate difference in risk of hypothesized injuries including more than one endpoint [38]. The Aalen Johansen estimator will be applied in the competing risks analysis. Endpoints included in the competing risk analysis are non-running-related injury causing a permanent stop of running and the 20 injuries presented by Taunton et al. [13] In the intensity group (Sch-I) the risk of achilles tendinopathy, gastrocnemius injuries, and plantar fasciitis are analyzed in a competing risk model, treating the remaining 17 injuries as competing events. In the volume group (Sch-V) the risk of patellofemoral pain syndrome, iliotibial band syndrome, and patellar tendinopathy are analyzed in a competing risk model, treating the remaining 17 injuries as competing events [21]. Differences are considered statistically significant at *p* < .05, and estimates are presented with 95 % confidence intervals. All analyzes are performed using STATA/SE version 13 (or more if applicable).

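### The intensity-by-volume interaction is listed as a tested hypothesis, but the two randomised schedules cannot identify it; only a non-randomised analysis of GPS-recorded running could address it

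*Protocol article*

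**What the plan says.** The last paragraph of the Background introduces its list with "The following hypotheses are tested (H"). The fourth entry (H4 below) is that "A positive excess risk due to interaction exists between running intensity and running volume". It adds that the effect should be stronger for pace-related injuries when speed changes more than volume, and stronger for distance-related injuries when volume changes more than speed. The paragraph that follows reserves the explorative label for analyses of the overuse questionnaire, so H4 stands on the tested side of the protocol's own division.

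The Methods randomise two groups. Under Intervention training period, Schedule Intensity (Sch-I) is described thus: "The total running volume per week is fixed, and only kilometers at a hard running pace follow the progression in running". Of Schedule Volume (Sch-V) it says: "Only the total running volume per week follows the progression in running". Before randomisation, "All included participants follow the same running schedule during the 8 week preconditioning period".

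Under Statistical analysis, the primary analysis of all data is instrumental-variable, and "The instrumental variable is the randomization". It continues: "Secondary analyzes are intention-to-treat and per-protocol".

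**The concern.** Excess risk due to interaction asks whether raising both exposures adds more risk than the two separate increases would add together. That takes information on runners who raise both and on runners who raise neither. The schedules progress one variable or the other.

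An estimate for H4 would therefore have to come from running that departs from the schedule. Who departs, and in which direction, plausibly depends on fitness, symptoms and motivation, and randomisation gives no protection against that. If H4 stays beside H1 as a tested hypothesis, under a statement that all data are analysed with randomisation as the instrument, a reader may give an observational interaction estimate the authority of a randomised result.

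**Working it through.** **1. The protocol's only sample-size figure.** Inputs from Power: 20 % (volume), 35 % (intensity), minimum difference 5 %, power 80 %. The p < .05 criterion is in Statistical analysis; two-sided is assumed. Reading the calculation as superiority by a margin:

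n per arm = [0.20 × 0.80 + 0.35 × 0.65] × (1.960 + 0.842)² / (0.15 − 0.05)² = 0.3875 × 7.85 / 0.01 ≈ 305, or 610 in total.

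This is within 3 % of the stated 620, and 620 × 1.15 = 713. The figure concerns the two-group risk difference. No calculation is given for H4.

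**2. What H4 needs.** Let R with two subscripts be the injury risk, the first subscript for intensity progressed (1) or not (0), the second for volume.

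- Interaction contrast: IC = R11 − R10 − R01 + R00
- Relative form: RERI = IC / R00

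**3. What is randomised (Tables 2 and 3).**

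| Cell | Supplied by |
|---|---|
| R10 (intensity only) | Sch-I: 18.5 km/week in the volume column for all 16 weeks, hard-pace km progress |
| R01 (volume only) | Sch-V: 18.5 rising to 24.5 km/week, 3 km moderate throughout, no hard pace |
| R11 (both) | no arm |
| R00 (neither) | no arm |

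In week 4 of Table 2 the pace entries add to 13.8 + 2.7 = 16.5 km, against 18.5 km in the volume column. The two need reconciling, but neither figure creates a missing cell.

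**4. Identifiability.** In the order (R00, R10, R01, R11), the arms give the rows (0,1,0,0) and (0,0,1,0), of rank 2. Adding the contrast (1,−1,−1,1) raises the rank to 3. The contrast lies outside what the arms can estimate, whatever the number of participants.

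**5. The instrument.** With arm Z as the only instrument and a linear model in intensity I, volume V and their product:

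E[Y | Z=1] − E[Y | Z=0] = βI·ΔI + βV·ΔV + βIV·Δ(I×V)

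Here Δ is the between-arm difference in mean exposure. That is one equation with three unknowns. The intention-to-treat and per-protocol analyses are also two-group contrasts.

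**6. How open the answer is.** With R10 = 0.35 and R01 = 0.20, IC = R11 + R00 − 0.55. R00 and R11 are assumptions, because the protocol gives neither.

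| R00 | R11 | IC | RERI |
|---|---|---|---|
| 0.05 | 0.35 | −0.15 | −3.0 |
| 0.05 | 0.60 | +0.10 | +2.0 |
| 0.10 | 0.45 | 0.00 | 0.0 |
| 0.20 | 0.35 | 0.00 | 0.0 |
| 0.20 | 0.60 | +0.25 | +1.25 |

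Over R00 from 0.05 to 0.20 and R11 from 0.35 to 0.60, the contrast runs from −0.15 to +0.25. Its sign rests wholly on the two risks that are not randomised.

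**7. For scale only.** Had 620 participants been spread over all four cells (155 each), power = Φ(IC/SE − 1.96), with SE² equal to the sum of R(1−R) over the cells, divided by 155. For R00 = 0.10 and R11 = 0.50 (IC 0.05) power is about 11 %. For 0.10 and 0.55 (IC 0.10) it is 31 %, and for 0.15 and 0.60 (IC 0.20) it is 82 %.

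**The case against.** The strongest reply is that H4 is not about the arms. H1 to H3 speak of a focus or a schedule, whereas H4 speaks of changes in speed and volume, which reads as a statement about running performed. GPS records kilometres and minutes per kilometre for each runner (Data on exposure; Discussion). This stands. A reader might infer that the trial cannot examine H4 in any way, and the documents do not support that: a non-randomised analysis is possible. What remains is that H4 is not labelled as such and falls under the statement that all data are analysed with randomisation as the instrument.

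Four further inferences go too far.

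- *No runner is ever scheduled to a joint or a no-change period.* This holds only for randomised progression over the 16 weeks. On entering week 1, Sch-I goes from 15 to 18.5 km and from 0 to 3 km hard, a joint change, and adaptation weeks schedule 0 % progression in both arms. These are not randomised cells, however. Sch-V makes the same 15 to 18.5 km step, so week 1 contrasts pace at equal volume, and adaptation weeks are tied to calendar time. Nor does the shared preconditioning period supply a randomised reference.
- *The within-arm competing-risk models fail H4.* They address the injury groups of H2 and H3, and nothing ties them to H4.
- *The protocol claims a confirmatory or powered test of H4.* It says only that the hypothesis is tested, and the aim stated in the abstract omits the interaction.
- *The lack of a described H4 model is an error.* This is a condensed article and the analysis plan is not shown, so that model may exist elsewhere. An analysis plan cannot, however, supply randomised cells that the design lacks.

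**Conclusion.** The point holds as one of identification and labelling. H4 is listed as tested beside hypotheses about the randomised schedules, yet the randomised comparison cannot identify it at any sample size: two of four risks are randomised, and a single binary instrument yields one equation for three effects. Only a non-randomised analysis of GPS-recorded running could address it, and that would be open to confounding.

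The conclusion rests on reading the exposures as progression over the 16-week intervention, on the schedules in Tables 2 and 3, and on arm being the only instrument, as stated. It does not depend on the values assumed for R00 and R11, which only show that the sign is undetermined. The primary outcome, H1 to H3, the sample size and the randomised comparison itself are untouched. What changes is what the trial may conclude about interaction.

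**What to change.** Either take H4 off the list of hypotheses tested by the randomised comparison, or keep it under an explicit label: an exploratory, observational analysis of GPS-measured changes in running volume and pace, exempt from the instrumental-variable statement in Statistical analysis.

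If it is kept:

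- State how changes in volume and pace are defined from the GPS records, including what counts as both and as neither.
- Adjust for the baseline factors already collected: BMI, age, gender, previous injury, running experience and general activity level.
- Do not simply add weekly symptoms as a covariate. They may confound later running and also result from earlier running, so ordinary adjustment could remove part of the effect sought. Use a method suited to time-varying confounding, such as inverse-probability weighting of a marginal structural model, or confine symptoms to a sensitivity analysis.
- Report estimates with confidence intervals and make no randomised or confirmatory claim.

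The cost is small. H4 loses its tested status and some analysis work is added. No participants, data collection or trial procedures change.

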## Methods/design

The Run Clever trial is a randomized trial with a 24 - week follow-up. The follow-up period is divided into an 8 - week *Preconditioning* period and a 16 - week *Intervention Training* period. The randomization is performed after the 8 - week preconditioning period (Fig. 1). Participants are randomly allocated into two intervention groups, following different running schedules: Schedule Intensity (Sch-I) and Schedule Volume (Sch-V). The main outcome is injury and the physiotherapists diagnosing injured participants (diagnostic team) are blinded to group allocation.

**Fig. 1 Fig1:**
[figure not shown]
Flow-chart of outline of the RUN CLEVER trial

### Study population

The target population is recreational runners, defined as a person averaging between 1 and 3 weekly running sessions the past 6 months. Notice of the trial is distributed through social media, running magazines, recreational running clubs who are members of the Danish Athletic Federation (DAF), the Danish recreational sports association (DGI) and by handing out flyers at recreational running events. Persons interested, register at the trial homepage [26] and are asked to answer an online inclusion/exclusion questionnaire. Answers will be assessed by the investigators and eligible persons are included based on the inclusion and exclusion criteria.

### Inclusion and exclusion criteria

Healthy persons who own an IOS- or Android-based smart-phone, between 18 and 65 years, with an average of 1 – 3 weekly running sessions the past 6 months are eligible for inclusion. Persons will be excluded if they have had an injury in the lower extremity 6 months preceding the baseline, or if any of the following contraindications for vigorous physical activity are present: Former heart or chest surgery, symptoms of chest pain, dizziness or discomfort when physically active, pregnant or taking prescribed medication related to cardiovascular problems, in accordance with the American College of Sports Medicine (ACSM) [27].

### Data collection

At inclusion participants are provided access to a personal internet-based training diary and an IOS- or Android-based smart-phone application (Help2Run). The personal internet-based training diary is hosted by Amazon, and backed-up by a Help2Run server placed in Hornslet, Denmark. Continuously during follow-up, participants upload data on exposure (running), outcome (injury) and other co-variates (weight and general physical activity during daily life). Participants use the personal training diary to get an overview of completed training, answer administered questionnaires and report injuries. Through the back-end system of the internet based training diary, the research group access and download data on running performed, symptoms reported and follow-up measurements. All downloaded data is saved on the internal server hosted by Aarhus University. Access to the back-end system is granted to members of the research group, but only after permission has been granted by the principal investigator. The system complies with the proper privacy and confidentiality procedures of handling medical and personal information.

